### Recruitment {15}

The study will be conducted at the following three hospitals: First Teaching Hospital of Tianjin University of Traditional Chinese Medicine, Changchun University of Chinese Medicine, and QILU Hospital of Shandong University. Participants diagnosed with ischemic stroke with aphasia will be recruited at three hospitals, mainly from clinical processes. Also, we will recruit subjects through posters and flyers. The subject screening will be completed at each center by experienced researchers. Informed consent of eligible patients was obtained and then randomized into groups.

## Assignment of interventions: allocation

### Sequence generation {16a}

The China Academy of Chinese Medical Sciences was commissioned to apply the “Central Randomization System for Clinical Research.” The 252 subjects will be randomly assigned to the experimental group and control group at 1:1 using the district-group randomization method.

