Name and contact information for the trial sponsor {5b}	Special funds from the central government of China
Role of sponsor {5c}	The sponsor provides funding to support the design of the study, execution, analysis, interpretation of the data, and decision to submit the results.

**Table 1 Tab1:** Trial registration data

Data category	Information
Registration number	ChiCTR1900026740
Date of last refreshed on	October 22, 2019
Date of registration	October 20, 2019
Registration status	Prospective registration
Public title	A randomized controlled trial for “Xing-Nao Kai-Qiao” Rehabilitation Program in the Treatment of Motor Aphasia after Stroke
Scientific title	A randomized controlled trial for “Xing-Nao Kai-Qiao” Rehabilitation Program in the Treatment of Motor Aphasia after Stroke
The registration number of the Partner Registry	AMCTR-IOR-19000302
Study leader	[name]
Study leader’s address	[name]
Approved no. of the ethics committee	TYLL2019[K]word015
Primary sponsor	The First Affiliated Hospital of Tianjin University of Traditional Chinese Medicine
Source(s) of funding	Central government special funds
Target disease	Aphasia after stroke
Study type	Interventional study
Study design	Parallel
Inclusion criteria	(1) Meet the diagnostic criteria for motor aphasia after stroke; (2) aphasia appears for the first time after stroke; (3) onset time ranged from 15 days to 3 months; (4) the severity of aphasia is 0–3, which can be used in conjunction with speech training; (5) consciousness of consciousness and stable vital signs; (6) aged 45 to 75 years old; (7) patient or family signed an informed consent form and have a good compliance
Exclusion criteria	(1) Combined with severe primary diseases such as liver, kidney, hematopoietic system, and endocrine system; (2) there are abnormalities in audio-visual, severe cognitive impairment, and mental illness, which cannot be combined with examination and treatment; (3) pregnant and lactating women
Recruiting time	From October 21, 2019, to December 31, 2020
Countries of recruitment	China
Primary outcomes	Western Aphasia Battery; Functional Language Communication Capability Check
Secondary outcomes	Boston Diagnostic Aphasia Examination; NIH Stroke Scale; SAQOL-39 Quality of Life Scale; Stroke-Specific Quality of Life Scale; the Health Scale of Traditional Chinese Medicine
Randomization procedure	Stratified block randomization method
Blinding	Open label

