## Methods: participants, interventions, and outcomes

### Study setting {9}

The patient data will be collected throughout the clinical trial in China at three level-III hospitals in Tianjin, Changchun, and Jinan.

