### Sample size {14}

Based on the previous pilot study, we expected that acupuncture combined with speech rehabilitation would be more effective than placebo combined with speech rehabilitation [6]. We were assuming that the difference in WAB-AQ values after treatment between acupuncture and placebo is 10.9, with a standard deviation of 22.9 in both groups. According to expert clinical observation, it was found that a superiority margin of 3 for comparisons of acupuncture and placebo for the primary outcome. We performed a superiority test to calculate the appropriate trial sample size with 80% power, *β* =0.2, and *α* = 0.05. The results showed that a clinically significant difference could be detected by a sample size of at least 105 in each group, allowing for a predicted 20% dropout rate. We plan to enroll 252 participants in this study.

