### Implementation {16c}

All subjects who meet the inclusion criteria and sign the informed consent form will be randomized. Requirements for randomization will be the responsibility of the investigator responsible for recruitment. The overall research group assigns the username and password to the quality control personnel in each sub-center. The quality control personnel logs into the central random system according to the respective username and password and applies for the random number online.

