## Data collection and management

### Plans for assessment and collection of outcomes {18a}

The original data include the patient’s baseline and medical documents of the subject, including outpatient medical records, inpatient medical records, and physical and chemical examination reports. Clinical research process documents include the informed consent form, screening form, inclusion form, medication record, laboratory record, and research case report form.

The scales used such as WAB, CFCP, BDAE, SAQOL-39 and SS-QOL, NIHSS, and HSTCM are all approved by the domestic and international industries. Two standardized trained physicians with the same criteria in each sub-center will perform the scale assessment to reduce variation between centers.

The quality supervisor will regularly verify the test process and check the authenticity of the data to ensure the quality of the test. Meanwhile, the data will be independently managed by a third party.

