## Statistical methods

### Statistical methods for primary and secondary outcomes {20a}

Baseline characteristics of patients were summarized in groups according to the study data. The chi-square test was used to compare categorical variables, and the 2-sample *t*-test or Wilcoxon rank-sum test was used to compare continuous variables. Analysis of variance for repeated measures was applied according to the outcome of the measurement time, or linear mixed models were used to analyze changes in measurements at different time points. Covariates such as age, duration of illness, and severity of aphasia will be included in the statistical model, correcting the effects of possible imbalances. If there is a violation of the distribution assumption, the appropriate transformation will be used.

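### Randomisation is registered as stratified but no stratum is named, and the listed covariates include neither centre nor any identified stratum

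*Protocol article*

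**What the plan says.** The allocation method is described in two places in the protocol article.

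- Table 1 (trial registration data), randomisation row: "Stratified block randomization method". No stratum is given.
- Sequence generation {16a}: the 252 subjects are "randomly assigned to the experimental group and control group at 1:1 using the district-group randomization method". Stratification is not mentioned.

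Numbers come from a central system, and each site has its own log-in. Under Implementation {16c}: "The overall research group assigns the username and password to the quality control personnel in each sub-center".

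The trial runs at "three level-III hospitals in Tianjin, Changchun, and Jinan" (Study setting {9}). Under Plans for assessment and collection of outcomes {18a}, two trained physicians in each sub-centre "will perform the scale assessment to reduce variation between centers".

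Statistical methods {20a} says: "Covariates such as age, duration of illness, and severity of aphasia will be included in the statistical model". The stated purpose is to correct for possible imbalances. Centre does not appear there, and none of the three covariates is described as a randomisation stratum.

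**The concern.** A reader cannot tell from the article whether allocation was balanced by centre, balanced by some other factor, or not stratified. That matters for the model. When allocation is stratified on a factor that predicts the outcome, the treatment contrast is protected from differences between strata. A model that omits the factor still counts those differences as residual noise, so its standard error is too large.

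Centre is the obvious candidate for such a factor. Raters are tied to centre, and the article itself expects variation between centres, which it addresses through rater training and common criteria. Nothing in the stated analysis commits to removing what remains. At stake are precision, interval width and some power.

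**Working it through.** **The passages side by side.** Table 1 says stratified. Sequence generation {16a} is silent on stratification and uses an unclear term, *district-group*, which could mean block or grouping by site. The per-site log-ins in {16c} make stratification by centre feasible but do not show that it was used. Three states remain open: stratified by centre; stratified by something else, possibly one of the three listed covariates; or not stratified.

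**The plan's own figure.** Sample size {14} assumes that "the difference in WAB-AQ values after treatment between acupuncture and placebo is 10.9", "with a standard deviation of 22.9 in both groups", with a superiority margin of 3, 80% power and α = 0.05. The effective difference is 10.9 − 3 = 7.9.

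- One-sided: n = 2 × 22.9² × (1.645 + 0.842)² / 7.9² ≈ 104 per arm by the normal approximation, and 105 by the noncentral t. This reproduces the stated 105.
- Two-sided: 132 (normal) or 133 (t), which does not.

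Size and power are therefore both computed one-sided at 5% below.

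**Effect of leaving out a stratifying centre.** Inputs from the article: 105 per arm, SD 22.9 (taken as the total SD, centre differences included), effective difference 7.9. Assumptions: centre is the stratum, there are three equal centres, the comparison is an unadjusted post-treatment one, and centre explains a share r of WAB-AQ variance. The article gives no value for r, so 0 to 20% is shown.

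- Standard error used when centre is ignored: 22.9 × √(2/105) = 3.16
- True standard error: 3.16 × √(1 − r)
- Ratio of the two: k = 1/√(1 − r)
- Actual size without centre: 1 − Φ(1.645 k)
- Power without centre: Φ(7.9/SE_true − 1.645 k)
- Power with centre: Φ(7.9/SE_true − 1.645)

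At r = 10%, SE_true = 3.00 and k = 1.054. Size is 1 − Φ(1.734) = 4.1%. Power is Φ(2.635 − 1.734) = 81.6% without centre and Φ(2.635 − 1.645) = 83.9% with it.

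| Centre share r | SE_true | Interval width ratio k | Size without centre | Power without centre | Power with centre |
|---|---|---|---|---|---|
| 0% | 3.16 | 1.000 | 5.0% | 80.4% | 80.4% |
| 5% | 3.08 | 1.026 | 4.6% | 81.0% | 82.1% |
| 10% | 3.00 | 1.054 | 4.1% | 81.6% | 83.9% |
| 20% | 2.83 | 1.118 | 3.3% | 83.0% | 87.5% |

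**Simulation check** (10,000 trials per setting, 35 per arm in each of three centres). At r = 10%, size is 4.1% without centre and 5.0% with it; power is 81.7% and 84.0%. At r = 20%, size is 3.0% and 4.9%; power is 82.2% and 87.1%. The 20% results lie slightly below the formula, by about two Monte Carlo standard errors at most.

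**The case against.** Several points on the other side are sound.

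- **No explicit contradiction.** A reader might infer that {16a} describes unstratified blocks and so conflicts with Table 1. It does not say that. A block method is compatible with stratified blocks, and Table 1 may simply be the fuller statement.
- **The model may already contain the strata.** A reader might infer that the strata are left out. Since none is named, any of the three listed covariates could be one.
- **The list is open.** It is introduced as examples, and a separate analysis plan may add centre.
- **An analysis without centre can be valid.** If allocation was not stratified, omitting centre matches the design, and adding it is a choice made for precision.
- **The size of the effect is hypothetical.** The centre share is assumed. The planned model is a repeated-measures or mixed model with severity as a covariate, and WAB is measured at baseline, so stable centre differences may be partly removed already.
- **Therapists.** Separate acupuncturists and language therapists at each site are plausible but not stated. Intervention description {11a} has the same people treating both arms, so therapist should not be confounded with treatment.

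These points rule out calling this a demonstrated contradiction or a threat to validity. They do not answer two things. Sequence generation {16a} sets out to state the method, yet leaves the registered stratification unexplained. And the statistical section chooses covariates without committing to the design factors in a trial whose raters differ by centre.

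**Conclusion.** The point holds as an inexpensive improvement. The article registers stratified randomisation, never says on what, and lists covariates that include neither centre nor any identified stratum.

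If centre was the stratum and is omitted, the test is conservative. For an assumed centre share of 5%, 10% or 20%, a one-sided 5% test runs at about 4.6%, 4.1% or 3.3%, and the power forgone is 82.1 − 81.0 = 1.1, 83.9 − 81.6 = 2.3 or 87.5 − 83.0 = 4.5 points. These figures rest on three equal centres, 105 per arm and an unadjusted post-treatment comparison; the planned model may gain less. If allocation was not stratified by centre, including centre would still recover some precision.

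A reader might infer a raised risk of false positives. The calculation shows the opposite direction: size falls below its nominal level.

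**What to change.** 1. In Sequence generation {16a}, state in standard terms the method and the strata actually used by the central system, and reconcile this with Table 1. The stratum should not be presumed to be centre, because Table 1 does not say so. Recruitment was due to end on 31 December 2020, before publication on 30 June 2022, so this is a matter of reporting what was done.
2. In Statistical methods {20a}, or in the analysis plan before unblinding, commit to centre and every actual stratification factor as fixed effects in the primary and secondary models, alongside the covariates already listed.

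The cost is wording plus 3 − 1 = 2 degrees of freedom for centre. With 210 evaluable patients, a simple two-group comparison would go from 208 to 206 residual degrees of freedom. Any further stratum not already in the model adds its own few. Sample size and conduct do not change.

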### Concealment mechanism {16b}

The participants will be randomized using the “Central Randomization System for Clinical Research.” The central randomization system was established to implement the allocation sequence and conceal the sequence until interventions are assigned. Throughout the study, Central will perform randomization and maintain the list, continuously blinded to data management and statisticians until the database is closed.

### Implementation {16c}

All subjects who meet the inclusion criteria and sign the informed consent form will be randomized. Requirements for randomization will be the responsibility of the investigator responsible for recruitment. The overall research group assigns the username and password to the quality control personnel in each sub-center. The quality control personnel logs into the central random system according to the respective username and password and applies for the random number online.

## Assignment of interventions: blinding

### Who will be blinded {17a}

Trial participants, outcome assessors, and statistical analysts will be blinded after being assigned to the intervention. Trial participants are randomly assigned. The outcome assessor enters the measurements into the computer, and the statistical analyst analyzes the data without access to the assignment information. The data will be reviewed in a blinded manner, entrusting the third-party (Guangdong Province Traditional Chinese Medical Hospital) medical statistics professionals to conduct statistical analysis.

### Procedure for unblinding if needed {17b}

Not applicable. Unblinding is not performed until the study is over.

## Data collection and management

### Plans for assessment and collection of outcomes {18a}

The original data include the patient’s baseline and medical documents of the subject, including outpatient medical records, inpatient medical records, and physical and chemical examination reports. Clinical research process documents include the informed consent form, screening form, inclusion form, medication record, laboratory record, and research case report form.

The scales used such as WAB, CFCP, BDAE, SAQOL-39 and SS-QOL, NIHSS, and HSTCM are all approved by the domestic and international industries. Two standardized trained physicians with the same criteria in each sub-center will perform the scale assessment to reduce variation between centers.

The quality supervisor will regularly verify the test process and check the authenticity of the data to ensure the quality of the test. Meanwhile, the data will be independently managed by a third party.

### Plans to promote participant retention and complete follow-up {18b}

The doctors in charge of the hospital follow up the patients by outpatient re-examination 6 weeks after the end of the treatment and 6 months after the onset time, performing scale measurement and medication evaluation, and collecting and storing the follow-up information of the patients. To reduce the rate of loss to follow-up, we will contact the patient or his/her family according to the follow-up date, make an appointment for the follow-up time, and give the patient a transportation subsidy of 100 yuan per person for each follow-up. If no contact can be made by telephone or at home, a loss to follow-up will be recorded. The causes of case dropout, discontinuation, and exclusion during the clinical trial shall be understood and documented in detail. The time of the last treatment will be recorded, and the items that can be evaluated will be completed.

### Data management {19}

All the data will be recorded in double versions using computer software, and different inputters will be trained. They will input the same case report and check with each other, and the two versions will be stored in the database.

Data collection shall be timely, complete, and accurate. After a blind audit of the data is conducted and the database established is deemed correct, the primary researcher and statistical analyst will lock the data. Researchers shall keep all study data until 5 years after the end of the study.

### Confidentiality {27}

All information related to the study will be securely stored at the study site. Information about all participants will be held in a restricted area. All data collection, processing, and management firms will be coded and classified to keep subject information confidential. All records containing names or other personal information, such as informed consent, will be kept separate from study records. This information will be kept in a specific area.

### Plans for collection, laboratory evaluation, and storage of biological specimens for genetic or molecular analysis in this trial/future use {33}

Not applicable. We will not design or collect biological specimens for genetic or molecular analysis in the current trial.

## Statistical methods

### Statistical methods for primary and secondary outcomes {20a}

Baseline characteristics of patients were summarized in groups according to the study data. The chi-square test was used to compare categorical variables, and the 2-sample *t*-test or Wilcoxon rank-sum test was used to compare continuous variables. Analysis of variance for repeated measures was applied according to the outcome of the measurement time, or linear mixed models were used to analyze changes in measurements at different time points. Covariates such as age, duration of illness, and severity of aphasia will be included in the statistical model, correcting the effects of possible imbalances. If there is a violation of the distribution assumption, the appropriate transformation will be used.

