**Methods:**

This is a multicenter randomized sham-controlled clinical trial. We will allocate 252 subjects aged between 45 and 75 years diagnosed with motor aphasia after stroke with an onset time ranging from 15 to 90 days into two groups randomly in a 1:1 ratio. Patients in the experimental group will be treated with “Xing-Nao Kai-Qiao” acupuncture therapy plus language training, and those in the control group will be treated with sham-acupoint (1 cun next to the acupoints) acupuncture therapy plus language training. All the patients will be given acupuncture and language training for 6 weeks, with a follow-up evaluation 6 weeks after the end of the treatment and 6 months after the onset time. The patients will mainly be evaluated using the Western Aphasia Battery and Chinese Functional Communication Profile, and the incidence of treatment-related adverse events at the 2nd, 4th, and 6th weeks of treatment will be recorded. The baseline characteristics of the patients will be summarized by group, the chi-squared test will be used to compare categorical variables, and repeated measures of analysis of variance or a linear mixed model will be applied to analyze the changes measured at different time points.

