### Outcomes {12}

#### Primary outcomes

The main observation was the difference between the two groups in WAB [17] scale scores and CFCP [18] scale scores after 6 weeks of treatment to assess the patients’ language abilities and functional communication abilities.

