### Methods in analysis to handle protocol non-adherence and any statistical methods to handle missing data {20c}

Data may be missing. Therefore, we will analyze data based on intention-to-treat analysis (ITT) and per-protocol analysis (PP) principles. We will also assess the robustness of the results of our research by comparing the results of the two datasets mentioned above to evaluate group effects.

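### The primary analysis is left as repeated-measures ANOVA or a mixed model with no week-6 contrast, and the ITT-versus-PP comparison does not address missing data

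*Protocol article*

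**What the plan says.** The Primary outcomes section sets the target: "The main observation was the difference between the two groups in WAB [17] scale scores and CFCP [18] scale scores after 6 weeks of treatment". The Sample size section plans a two-group comparison of post-treatment WAB-AQ: difference 10.9, SD 22.9, superiority margin 3, 80% power, 105 per group, 20% predicted dropout, 252 enrolled.

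The Statistical methods section {20a} gives the analysis as "Analysis of variance for repeated measures was applied according to the outcome of the measurement time, or linear mixed models were used". The abstract repeats the choice: "repeated measures of analysis of variance or a linear mixed model will be applied to analyze the changes measured at different time points". On adjustment, {20a} says "Covariates such as age, duration of illness, and severity of aphasia will be included in the statistical model".

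On incomplete data, section {20c} says "Data may be missing. Therefore, we will analyze data based on intention-to-treat analysis (ITT) and per-protocol analysis (PP) principles". It then treats the comparison of the two sets as the robustness check.

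On allocation, Table 1 (registration data) says "Stratified block randomization method", while Sequence generation {16a} says patients are "randomly assigned to the experimental group and control group at 1:1 using the district-group randomization method". Neither names a stratum. The sites are "three level-III hospitals in Tianjin, Changchun, and Jinan".

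**The concern.** The outcome and the sample size refer to one time point, but the analysis text refers to change over several. Two methods are allowed, and their default outputs answer different questions. A repeated-measures ANOVA reports a group effect averaged over the visits entered and a global group-by-time test. Neither is the week-6 difference, and neither can be set against a 3-point margin. With the choice open, the primary estimate could be settled after the data are seen.

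The second issue is incomplete data. Classical repeated-measures ANOVA discards any patient with a missed visit. Section {20c} promises ITT but offers only ITT against per-protocol as its answer to missing values. An unobserved week-6 score is unobserved in both sets, and the per-protocol set removes further patients, so agreement between them says nothing about the missing scores. Loss may be related to outcome, because the dropout criteria in the Eligibility section include deterioration and severe adverse reactions.

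The third issue is precision. WAB and CFCP are measured at baseline and there are three centres, but neither baseline score nor centre is named as a covariate.

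**Working it through.** **Inputs from the Sample size section.** Difference 10.9, SD 22.9 (taken as the SD of the week-6 score), margin 3, so net difference 10.9 − 3 = 7.9; alpha 0.05 with sidedness not stated; power 0.80; 105 per group; 20% dropout; 252 enrolled, or 126 per arm.

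**Step 1: reproduce the plan's figure.** n per group = 2 × (22.9/7.9)² × (1.645 + 0.842)² ≈ 104 with one-sided alpha 0.05. The noncentral-t version gives 105 (power 0.801), as stated. Two-sided alpha with the margin gives 132. Without the margin the result is 55 (one-sided) or 70 (two-sided). The stated enrolment is 105 × 1.2 = 126 per arm. The calculation is therefore a single-time-point comparison, with no repeated-measures term and no baseline adjustment. With 126 × 0.8 = 100.8 per arm observed, its power is 0.79 (one-sided 0.05, margin 3).

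**Step 2: what the ANOVA main effect would estimate.** The article gives no trajectory and does not say which visits enter the model, so these are assumed scenarios.
- Linear rise, weeks 0, 2, 4, 6: (0 + 3.63 + 7.27 + 10.9)/4 = 5.45, half the week-6 difference.
- Late onset, weeks 0 to 6: (0 + 0 + 5.45 + 10.9)/4 = 4.09.
- Linear rise, weeks 2 to 6 only: (3.63 + 7.27 + 10.9)/3 = 7.27.
- Linear rise then held, all six visits: (0 + 3.63 + 7.27 + 3 × 10.9)/6 = 7.27.

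For k visits with common correlation ρ, the SD of a patient's mean is 22.9 × √[(1 + (k − 1)ρ)/k]. At 100.8 per arm, two-sided 0.05 and no margin, the main effect in the first scenario has power 0.57, 0.48 and 0.45 at ρ = 0.5, 0.7 and 0.8. The plain week-6 comparison has 0.92 on the same basis. In the six-visit scenario the figures are 0.84, 0.74 and 0.69.

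**Step 3: cost of requiring complete visits.** Assume 3% to 5% of visits are missed independently, on top of the stated 20% dropout. Patients complete at weeks 2, 4 and 6 number 100.8 × 0.97³ = 92.0 down to 100.8 × 0.95³ = 86.4 per arm. Power is then 0.76 to 0.73 (one-sided 0.05, margin 3). Those with a week-6 score number 100.8 × 0.97 = 97.8 down to 100.8 × 0.95 = 95.8. A mixed model would also use the partial records.

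**Step 4: possible completer bias.** If completers and dropouts differ by the same gap in both arms, bias = gap × difference in dropout rates. With assumed dropout of 25% and 15%, a gap of 5 to 15 points gives 0.5 to 1.5 points. The direction depends on which arm loses more. With equal dropout it is zero.

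**Step 5: value of baseline adjustment.** Residual SD = 22.9 × √(1 − r²), where r is the assumed correlation between baseline and week 6. Power is at 100.8 per arm, one-sided 0.05, margin 3.
- r = 0.5: SD 19.8, power 0.88, n per group for 80% power 78.
- r = 0.6: SD 18.3, power 0.92, n 67.
- r = 0.7: SD 16.4, power 0.96, n 53.

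The comparator is 0.79 with no adjustment. Severity of aphasia is already planned as a covariate, so the true increment is smaller to the extent that it captures the baseline score.

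**The case against.** The strongest reply is that one of the two permitted methods is sound. A linear mixed model keeps patients with partial data and can yield a week-6 contrast. The Primary outcomes section already fixes the time point, and a full covariate list, covariance structure and sensitivity analyses commonly belong in an analysis plan, which is not shown. All of that stands. It does not remove the either/or in the text, or the reliance on ITT against per-protocol as the answer to missing data.

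Four stronger readings are tempting, and the document does not support them.
- A reader might infer that repeated-measures ANOVA cannot give the week-6 difference. A contrast can be taken after it; the accurate statement is that none is specified. The dilution in Step 2 applies only if the main effect were reported as primary.
- A reader might infer that baseline score and centre are excluded. The covariate list is open and includes severity of aphasia, probably the 0–3 grade used for eligibility, and the week-0 score may enter as a repeated measure. They are unnamed, not ruled out.
- A reader might infer that ignoring the strata makes the standard error wrong. The strata are never defined, so this cannot be checked. Only the absence of centre can be.
- A reader might start from a power of 0.69, which is the two-sided 0.05 figure with the margin. The stated 105 reproduces only at one-sided 0.05, where the starting point is 0.79.

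The retention section {18b} also partly covers patients who stop: it provides for follow-up contact, travel support and completing whatever can still be assessed. It does not clearly commit to a week-6 score. That dropout depends on outcome is plausible from the dropout criteria but is not established.

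**Conclusion.** The concern holds in this form. The article leaves the primary method as an unresolved choice, names no contrast for the week-6 difference on which the trial is defined and sized, allows a complete-visit method alongside an ITT commitment, and offers a missing-data check that cannot do that job. Not naming baseline score and centre is a secondary weakness that costs precision.

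The sizes are illustrations. The ANOVA main effect would be 4.09 to 7.27 points against 10.9, depending on the assumed trajectory and visits. Requiring complete visits would leave 86 to 92 of 126 per arm through week 6, given the stated dropout and an assumed 3% to 5% of missed visits. Baseline adjustment would raise power from 0.79 to 0.88–0.96 at r = 0.5 to 0.7, less whatever severity already explains. The completer-bias figure rests wholly on assumed inputs and has no known direction. The need to fix one method and one contrast depends on none of these assumptions.

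**What to change.** Delete the repeated-measures ANOVA option and state one primary model:
- a linear mixed model for repeated measures on post-baseline scores at weeks 2, 4 and 6, in all randomised patients as randomised;
- terms for arm × visit, baseline score of the same scale × visit, centre and any factor actually used to stratify, plus the already planned age, duration of illness and severity of aphasia as a closed list;
- the arm contrast at week 6 as the primary estimate. For WAB-AQ, compare its confidence limit with the 3-point margin and state the sidedness. Use the same model for CFCP with baseline CFCP; the article derives the margin for WAB-AQ only, so say what the CFCP contrast is compared with.

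State that week-6 scores are also sought from patients who stop treatment. Keep per-protocol as supportive, and replace its comparison with ITT as the missing-data check by a delta-shift sensitivity analysis.

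The cost is wording and slightly more analysis work; the week-6 visit is already scheduled. The planned end of recruitment (31 December 2020) precedes publication (30 June 2022). If data collection has ended, the request for extra week-6 scores can no longer be met, but the model and contrast can still be fixed before unblinding.
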